### Outcomes

Primary outcome: The reductive ratio of HAMD-17 after 4 weeks, as well as after 20 sessions.

Secondary outcomes: The changes in other clinical assessments such as the Young Mania Rating Scale (YMRS), Clinical Global Impression Scale (CGI), cognitive function, biomarkers representing potential mechanisms associated with TRD, and neuronal activity measured using rs-fMRI.

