### Sample size

The sample size was calculated based on the data from O’Doherty et al. (2001) [11] and Cieslik et al. (2013) [16]. In these studies, active tDCS was assumed to be superior to sham tDCS in controlling depression with a conservative mean difference of 0.65 and standard deviation (SD) = 0.25. We set a type 1 error α (significance) and a power of 80%. The G power software (V3.1.9.4) was used to calculate the sample size. The results indicated a minimum requirement of 24 participants per group (a total of 72 participants). Accounting for a 20% dropout rate, 87 participants are required for our experiment. Finally, we plan to enroll 30 participants per group for a total of 90 participants.

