### Data collection methods

#### Primary study parameter/endpoint

*HAMD-17*: The primary outcome criterion is the reductive ratio of the HAMD-17 score after one, two and 4 weeks of treatment. Treatment response is defined as a 50% reduction in the HAMD-17 score, and remission as a 75% reduction at any point during the 12-week trial compared with the baseline.

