### Statistical methods

Descriptive analyses will consist of means and SD for continuous variables and percentages for categorical variables. Data normality will be tested with the results expressed as mean ± SD or percentage, whenever appropriate. Nonparametric tests are to be used if the data are not normally distributed. Baseline variables will be compared between the groups using either the Student’s t-test or chi-squared test (e.g., sociodemographic data, cognitive function data, biomarkers representing inflammatory mechanisms associated with TRD, and response and remission rates among groups). To compare the primary endpoint, a two-way ANOVA will be used, considering the group (intervention and sham control groups) and time points (pre- and post-intervention), followed by the Bonferroni post hoc test, in case of significant F-ratios. A mixed-effects model for repeated measures will analyze changes from baseline HAMD-17 scores, time, and their interaction. Pretreatment values (e.g., age, sex, baseline HAMD-17, and biomarker levels) will be adopted as covariates to correct for possible differences. An intention-to-treat analysis will be conducted, that is, all participants will be included in the final analysis regardless of adherence to the intervention. No additional analyses will be performed for this study. All calculations are to be performed using R software (version 4.1.3), and the significance level is set at *p* ≤ 0.05.

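### The pre/post ANOVA named for the primary endpoint does not by itself deliver the stated intention-to-treat analysis; the repeated-measures model already listed should carry the primary inference

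*Protocol article*

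**What the plan says.** All of the key statements stand in one paragraph, Statistical methods.

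- **Primary test.** "To compare the primary endpoint, a two-way ANOVA will be used", with group as one factor and two levels of time, before and after the intervention, as the other. A Bonferroni post hoc test follows a significant F.
- **Second model.** "A mixed-effects model for repeated measures will analyze changes from baseline HAMD-17 scores, time, and their interaction". This sentence does not mention the primary endpoint and does not list group among the terms. Baseline HAMD-17, age, sex and biomarker levels are then named as covariates, without saying for which model.
- **Analysis set.** Intention-to-treat, explained as "all participants will be included in the final analysis regardless of adherence to the intervention".
- **Anything further.** "No additional analyses will be performed for this study".

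Two other sections bear on the point. Outcomes gives the primary outcome as "The reductive ratio of HAMD-17 after 4 weeks, as well as after 20 sessions", while Primary study parameter/endpoint says "The primary outcome criterion is the reductive ratio of the HAMD-17 score after one, two and 4 weeks of treatment", so HAMD-17 is planned at weeks 1 and 2 as well as week 4. Sample size states a minimum of 24 per group (72 in total), then "Accounting for a 20% dropout rate, 87 participants are required for our experiment", and settles on 90.

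**The concern.** The analysis set and the primary test do not fit together. A pre/post comparison needs a post value. Discontinuation or modifications lists ways out of the study, such as withdrawal by the participant or serious physical disease, after which a week-4 rating may not be obtainable. Such a participant adds nothing to the treatment contrast of the named test, even if weeks 1 and 2 were rated.

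With 20 weekday sessions of 60 minutes, leaving may well depend on early response or tolerability, and this may differ between active and sham stimulation. A comparison of those who stayed would then be biased while being reported as intention-to-treat. The plan already contains a model that would reduce this problem, but it does not say which of the two models decides the trial.

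**Working it through.** **1. Who informs the ANOVA contrast.** For one active arm A against sham S, the group-by-time term estimates

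(mean post − mean pre in A) − (mean post − mean pre in S).

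- Run on complete pairs, a participant without a post score is removed altogether.
- Run on rows, the baseline row stays in, but the post mean is still a mean over those who have a post score.
- Either way, scores at weeks 1 and 2 do not enter, because time has only two levels.
- Only imputation would bring the participant into the post mean. The article neither states nor excludes it.

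**2. Who informs the repeated-measures model.** A likelihood-based model on visits at weeks 1, 2 and 4 keeps anyone with a baseline and at least one later score. To answer the trial's question it needs arm and arm-by-visit terms, and the sentence as written does not name group.

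**3. How many participants are at stake.** Inputs from Sample size: 72 needed, 20% dropout, 90 enrolled.

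- The plan's 87 is reproduced as 72 × 1.2 = 86.4, rounded up.
- Dividing by the retained fraction gives 72 / 0.8 = 90, which equals planned enrolment.
- 90 × 0.8 = 72 retained, so 90 − 72 = 18 lost, or 18 / 3 = 6 per group.

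The 18 is an upper figure. The 20% is not tied to a visit, the study runs 12 weeks (Trial design), and the primary endpoint falls at week 4. Anyone lost after week 4 already has the score. The 24 per group is taken as given here; whether it follows from the stated effect and SD is a separate matter.

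**4. Possible bias.** The document gives no HAMD-17 effect in points, no correlations between visits and no dropout mechanism, so these are assumptions: true benefit 3 points, SDs 4 to 6, between-visit correlations 0.4 to 0.75, and dropout after week 2 depending on the week-2 score. Simulation with 400,000 per arm gave:

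| Dropout pattern | Completers only | Using weeks 1 and 2 |
|---|---|---|
| Same mechanism in both arms | 3.01 | 3.02 |
| Non-responders leave, 25% sham and 15% active | 2.78 | 2.98 |
| Non-responders leave in one arm only | 2.54 | 2.98 |
| The reverse | 3.42 | 2.99 |
| Non-responders leave one arm, early responders the other | 2.34 | 3.01 |
| The reverse | 3.67 | 3.00 |

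Bias against 3 is about 0 in the first row, 3 − 2.78 = 0.22 in the second, 0.46 and 0.42 in the next two, and 0.66 and 0.67 in the last two (0.67 / 3 = 22%). Other settings within the same ranges gave 3.03, 2.81, 2.55 and 3.43 for the first four rows. They gave 2.13 and 3.86 for the last two, so the most extreme pattern can reach about 0.9.

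**The case against.** The strongest reply is that the plan already contains the remedy: the mixed model sits in the same paragraph, and early scores are ignored by the ANOVA, not by the plan as a whole. That is right, and it makes this a question of which model leads rather than of a missing method. It does not remove the point. The sentence that mentions the primary endpoint names the ANOVA, and with missing data the two models rest on different participants.

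Four further replies deserve weight.

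- *The primary result will be a completer analysis.* A reader might infer this, but the document does not say so. It nowhere restricts the analysis to completers, and imputation rules may stand in a fuller document. Their absence from an article is no fault.
- *The dropout allowance contradicts intention-to-treat.* A reader might infer this too. It does not: enrolling extra participants protects power and is not an exclusion rule. Sample size calls 72 a minimum and does not limit the analysis to 72.
- *The intention-to-treat sentence is about adherence.* True: someone who misses sessions can still be rated at week 4. The sentence nevertheless says that all participants are included, and the named test cannot do this alone for those with no post score.
- *The bias figures are built on assumptions.* True. The larger ones need dropout in one arm only or opposite mechanisms. The near-unbiased right-hand column follows from simulating dropout that depends on an observed score, which is the condition under which that estimate works.

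**Conclusion.** The point stands as a mismatch within Statistical methods. Without imputation, the test named for the primary endpoint draws its contrast only from participants with a post-intervention score, and the listed model that would use the other HAMD-17 scores is not given the primary inference. Up to about 18 of 90 participants are concerned at the stated dropout, fewer if some of it comes after week 4.

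The effect on the estimate cannot be read from the document. Under the illustrative assumptions it is nil when dropout works alike in the arms and about 0.2 to 0.7 points on a 3-point benefit, in either direction, when it differs. This is a cheap improvement worth making before unblinding. It is not evidence that the trial's result will be biased.

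**What to change.** In Statistical methods:

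1. Make the repeated-measures model already listed the primary analysis. Use HAMD-17 at weeks 1, 2 and 4, with randomised arm, visit, arm-by-visit and baseline HAMD-17. Include every randomised participant with a baseline and at least one later score, and read each active-versus-sham contrast at week 4.
2. Drop the pre/post ANOVA as the primary test.
3. Amend the sentence that rules out additional analyses so that it allows one missing-data sensitivity analysis in which dropouts are assumed to do worse. Participants who leave before the week-1 rating do not enter the primary model, so this analysis should cover them.

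Sample size needs no change on this account.

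The cost is a few sentences and a little more analysis. No new patients or visits are needed, since weeks 1 and 2 are already rated. The price is reliance on missing-at-random given the observed scores, which is a weaker assumption than the one a comparison of completers makes.

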### Harms

All side effects for each participant will be recorded and reported throughout the study using a serious adverse event reporting system. It is unlikely that the participants in this trial will experience serious adverse events (SAEs) or serious adverse reactions. Common adverse reactions include dizziness, headache, and tingling of the scalp. Only unexpected serious adverse events or reactions unrelated to these clinical procedures will be reported as SAEs.

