### Discontinuation or modifications

Participants can leave the study at any time for any of the following reasons:If participants do not meet the inclusion criteria;If participants or their guardians decide to leave the study;If participants develop a serious physical disease whether or not it is related to tDCS;If participants stop taking their medication for three consecutive days, stop effective contraception, or become pregnant;If participants use other treatments (including MECT, rTMS);If other conditions occur, and the investigator decides to terminate the study;If the participant fails to comply with the study procedures.

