### Data monitoring

A Data Monitoring Committee (DMC) has been established. The DMC is independent of the study organizers. Interim analyses of the primary endpoint when 30 and 70% of patients have been randomised and have completed the 12-week follow-up, respectively, will be performed by an independent statistician, who will report independently to the DMC.

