## Discussion

In this randomized double-blinded sham-controlled trial, we aim to determine the effectiveness of adjunctive intensive tDCS with positive stimulation of the left DLPFC or negative stimulation of the OFC on depressive symptoms in patients with TRD. In addition to their usual treatment, participants will be randomly assigned to receive either 20 weekday sessions of active DLPFC tDCS, active OFC tDCS, or sham tDCS as adjunctive treatment. We will regularly assess depression severity and functional impact using the HAMD-17, MADRS, ODQ, YMRS, CGI, and SDS throughout the trial. We will assess cognitive changes using the WCST and SCWT. Moreover, participants will be regularly assessed for treatment-related side effects using validated scales.

As OFC tDCS could have benefits in behavioral decision making and negative reinforcement; and DLPFC tDCS might improve memory, underload syndrome, and interest declination; the study will examine how depressive symptoms change in participants with TRD treated by DLPFC or OFC tDCS throughout the trial period. Entry and exit interviews will be recorded and analyzed by the staff of this research team at the Shanghai Mental Health Center.

This study has numerous strengths and will follow the Consolidated Standards of Reporting Trials (CONSORT) 2010 statement on design and reporting [17]. Using REDCap to randomly assign participants to treatment groups will ensure that the allocation is concealed, documented, and unchangeable. To minimize the placebo effect, both the participants and the treating investigators will be blinded. Primary and secondary outcomes were chosen to capture a range of subjective, objective, and functional measurements of depression severity, and the regular use of adverse event scales will ensure that the treatment side effects will be adequately captured. Measurements will also be taken at multiple points during and after the trial to better describe the overall course and persistence of treatment-related effects.

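### As worded, the SAE rule withholds SAE status from at least some serious events caused by stimulation, and it conflicts with the opening of its own section

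*Protocol article*

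**What the plan says.** The Harms section of the protocol article has four sentences, and all four bear on this point.

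1. The general recording rule: "All side effects for each participant will be recorded and reported throughout the study using a serious adverse event reporting system".
2. The expected frequency of serious events: "It is unlikely that the participants in this trial will experience serious adverse events (SAEs) or serious adverse reactions".
3. The reactions the investigators anticipate: "Common adverse reactions include dizziness, headache, and tingling of the scalp".
4. The SAE rule itself: "Only unexpected serious adverse events or reactions unrelated to these clinical procedures will be reported as SAEs".

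Two other places touch on the subject. Under Discontinuation or modifications, one reason for leaving the study is worded without regard to causality: "If participants develop a serious physical disease whether or not it is related to tDCS". The Discussion relies on rating scales for harms and states that "the regular use of adverse event scales will ensure that the treatment side effects will be adequately captured". Neither place changes or qualifies the SAE rule.

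**The concern.** What makes an adverse event an SAE is its seriousness. Whether it was expected and whether the intervention caused it are judgements made about the event afterwards. The last sentence of the Harms section uses both judgements as entry conditions, and the relatedness condition points the wrong way: being *unrelated* is what qualifies an event. Followed literally, the rule leaves out of the SAE record the serious events that a sham-controlled trial of a device most needs to see.

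The article's own description of the intervention adds weight. The Background gives 20 to 30 minutes as the typical length of a tDCS session. Here each session lasts 60 minutes, and there are 20 of them. The Abstract says that OFC stimulation as adjuvant treatment in this population has seldom been studied. Two of the three arms, 30 + 30 = 60 of the 90 planned participants, receive active stimulation. Serious related events may well be rare, but existing knowledge about them is thin, so how they are classified matters.

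**Working it through.** No figure is involved, so the check is a reading of the sentence against every combination of the two filters, and then against the other harms text.

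**Step 1: the readings.**

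- Reading A (natural): *unexpected* and *unrelated* both qualify events and reactions alike. A serious event is reported as an SAE only if it is unexpected **and** unrelated.
- Reading B (split): the sentence names two categories, unexpected serious adverse events of any cause, **or** reactions that are unrelated to the procedures.

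**Step 2: what each reading reports as an SAE.**

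| Serious event is | Reading A | Reading B |
|---|---|---|
| Unexpected, unrelated | Reported | Reported |
| Unexpected, related to stimulation | Not reported | Reported |
| Expected, unrelated | Not reported | Reported only if an unrelated event may be called a reaction |
| Expected, related to stimulation | Not reported | Not reported |

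Reading A reports 1 of 4 combinations and excludes both related ones. Reading B reports 2 or 3 of 4, depending on how loosely *reaction* is taken. The expected-and-related combination is excluded under both, so neither reading reports every serious stimulation-related event as an SAE.

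**Step 3: internal consistency of the sentence.** A reaction is an event attributed to the intervention. Requiring it to be unrelated leaves a category that is empty if the term is used strictly. In addition, the procedures the sentence refers to are not identified anywhere in the section. Stimulation is the likely referent, because the sentence just before lists its common reactions.

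**Step 4: against the first sentence of the section.** That sentence sends all side effects, without exception, into a serious adverse event reporting system. The last sentence then admits only a subset as SAEs. A serious side effect of stimulation is covered by the first sentence and, under Reading A, shut out by the last. The section does not say which governs.

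**Step 5: against the other places.** Under Discontinuation or modifications, a serious physical illness can end participation whatever its relation to tDCS. Under Reading A, an illness of that kind caused by tDCS could therefore be a reason for leaving the study and yet not be an SAE. The aim of adequate capture in the Discussion concerns side effects collected on scales and does not say how a serious event is classified.

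**The case against.** The best defence is that nothing need go unrecorded. The first sentence of the section covers all side effects and the Discussion adds regular adverse event scales, so a serious event caused by stimulation would still be in the trial's data. That stands. It limits the point to SAE classification and reporting; it would be wrong to say that such events disappear from the trial.

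A second defence is that this is a slip of wording. Coming straight after the list of dizziness, headache and scalp tingling, the sentence may have been meant only to say that these common reactions are not SAEs. That is plausible, and under Reading B the excluded group could be small, because the section lists no serious event as expected. But the sentence does not say this, and staff will apply it as written. Nor can the gap be left to a fuller protocol: the article does not omit the rule, it states one, with a limiting *only*.

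Some stronger conclusions are tempting but are not supported:

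- A reader might infer that the data monitoring committee would see a truncated SAE count. The Data monitoring section says "A Data Monitoring Committee (DMC) has been established" and gives it interim analyses of the primary endpoint. It neither describes nor restricts the safety data the committee receives.
- A reader might infer a biased active-versus-sham comparison of SAEs. The Statistical methods section specifies no such comparison.
- A reader might infer that a suicide attempt would be dropped as expected from the illness. Nothing in the article classes it as expected; if it were unexpected and unrelated to stimulation, even Reading A would report it.
- A reader might want a probability that an event is missed. The article gives no SAE risk, calls such events unlikely, and offers no basis for choosing a rate.

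**Conclusion.** The point holds as an error in a stated rule. On its natural reading, the SAE rule denies SAE status to every serious event caused by stimulation. On the alternative reading it still denies it to those that are expected. The sentence contradicts itself and conflicts with the first sentence of its section, and nothing elsewhere in the article repairs it. The consequence is that the trial's SAE count could understate harm from stimulation, although the events themselves should remain recorded as side effects.

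The size can be stated only in categories: three of four combinations excluded under Reading A, one or two of four under Reading B. This rests on taking the unnamed procedures to be, or to include, the stimulation sessions. That the rule excludes *all* related serious events rests on Reading A, the more natural but not the only possible reading. That it excludes *some* holds under both. Because the rule governs how serious harm is reported and the correction is cheap, it should be made.

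**What to change.** Reconcile the first and last sentences of the Harms section by replacing the last one. Suggested content:

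- Every serious adverse event is reported as an SAE, whatever its expectedness and whatever its relationship to tDCS.
- Relatedness and expectedness are recorded for each SAE as attributes and are not used to decide whether it is reported as one.
- Dizziness, headache and scalp tingling, when not serious, are recorded as adverse events. This is stated separately, so that the probable intent of the present sentence is kept without narrowing the SAE definition.

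The cost is one amended sentence, made through the formal amendment that the Protocol amendments section already requires, and possibly a few more SAE forms. It changes nothing in stimulation, visits, outcomes or sample size.

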### Auditing

The principal investigator (PI) WH will be responsible for the ongoing management of the study. The sponsor will monitor and conduct audits on a selection of studies in its clinical research portfolio. Monitoring and auditing will be conducted in accordance with the sponsor’s monitoring and audit procedures.

